### Recruitment and Enrollment Procedures

Recruitment will be led by a Thai transgender woman researcher with 5 years of experience developing materials and recruiting young transgender women for HIV prevention research. Materials will be placed at physical and online venues, including study clinical sites and community venues that serve transgender women (eg, health centers, bars and clubs, and community organizations). Participants will also be recruited by paid study recruiters who identify as transgender women using direct outreach in the community. These efforts have been successful in other projects seeking to enroll transgender women [26,54,55], and as such, we do not anticipate having problems reaching our target sample.

Potential participants will complete a prescreener over the phone or in person. If eligible and interested in participating, the transgender women will complete an in-person screening at one of the study clinics. After providing verbal consent, they will complete a prebaseline survey assessing basic demographic information, history of HIV and STIs, HIV testing, access to HIV and STI diagnostic and treatment services, recent sexual behavior, use of PrEP, and knowledge and acceptance of PrEP. They will undergo HIV testing (with a fourth-generation serum) and screening for hepatitis B (with surface antigens and antibodies), hepatitis C (with antibodies), and renal insufficiency (with serum creatinine testing) to confirm their eligibility for PrEP and the study. Research staff will determine if the transgender women meet the inclusion criteria and have completed informed consent. The screening visit, enrollment, and baseline assessment should occur on the same day, or failing that, within one week. After signed consent is obtained, participants will be asked to provide contact information for a family member or friend who can be called if they cannot be reached.

### Data Collection Tools and Procedures

Self-report measures will be administered using the cloud-based CASI system in Thai at baseline, immediately postintervention at the end of the first month, and at 3, 6, 9 and 12 months. In CASI, the participant sees each question and a list of responses on a private iPad screen. The response is entered by pressing a number keypad. The data are stored directly in the password-protected Qualtrics system. CASI elicits more valid and reliable data than face-to-face or written questionnaires [56-58]. The topics we assess are sensitive; CASI allows greater privacy for honest responses [59,60] and reduces missing data and interviewer bias. Our team has been using Qualtrics for CASI for over 8 years.

The primary acceptability outcome will be measured by the System Usability Scale, a 10-item Likert scale giving an overall view of subjective assessments of usability. The System Usability Scale is technology agnostic and provides a global measure of system satisfaction [61]. A score of >50 (out of 100) indicates that an intervention is acceptable [62]. We will also assess interest in future use at study completion. For feasibility, we will assess the number of responses and frequency of usage of Enhanced YaCool, the number of MES-PrEP sessions completed, cumulative time spent in MES-PrEP, and recruitment rates. PrEP uptake will be assessed using self-reported measures (from participants who left the clinic with an emtricitabine/tenofovir disoproxil fumarate [TDF/FTC] prescription), confirmed via chart review and pharmacy records. Adherence to PrEP will be measured using (1) a young adult adherence interview with a visual analog scale [63]; (2) a 4-week percentage taken measure (answering the question “What percentage of the time were you able to take all your PrEP medications in the past 4 weeks?”) [64]; and (3) biological testing using a DBS report on 80% TDF/FTC adherence after at least 3 weeks of regular adherence. The results of DBS testing will be triangulated with the self-reports. We will assess IMB model constructs—knowledge, attitudes, motivations, and behavioral skills related to taking PrEP, and important contextual factors (age, education, depression, and PrEP-related stigma).

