### Study Aims

In the proposed study, we will develop 2 potentially synergistic, technology-based, theory-driven interventions aimed at maximizing PrEP usage. We propose to develop and pilot a multi-component, technology-based intervention based on the principles of MI to promote PrEP usage. This process will include 2 guiding frameworks: the ADAPT-ITT (assessment, decision, adaptation, production, topical experts, integration, training, testing) model of intervention adaptation, and a multiphase optimization strategy (MOST) design to identify the most effective culturally and developmentally tailored intervention to address PrEP usage in this population. In phase I (R21), we will adapt an existing 2-session, technology-delivered, MI-based intervention to focus on PrEP uptake and adherence in Thai transgender women who are HIV negative through a systematic, multi-step process [38] to develop what we term the Motivational Enhancement System for PrEP Uptake and Adherence (MES-PrEP). MES-PrEP sessions will be completed on participants’ internet-connected mobile devices (eg, smartphones) while at clinics for this study. We will also refine and enhance YaCool, a mobile app with integrated text messaging developed and used clinically by our Thai team. The refined version is called Enhanced YaCool and will enable self-management of gender and sexual health (including PrEP) in transgender women. These intervention components will be integrated to enhance the impact of a 2-session intervention through daily health self-management. In phase II (R33), we will utilize a MOST framework with a factorial design to efficiently identify the most effective component or combination of components to promote PrEP uptake and adherence in young Thai transgender women. This study may pave the way to scaled-up PrEP implementation, a crucial step in eliminating the HIV epidemic among transgender women in Thailand.

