### The Intervention Components

#### MES-PrEP Intervention

MES-PrEP is a brief, tailored, 2-session intervention deliverable to any internet-enabled device via the Computerized Intervention Authoring System (version 3.0). A 3D avatar speaks, moves, and displays emotions. At the start of each session, the participant chooses an avatar, who delivers the intervention in a way that closely follows the most recent edition of MI (MI-3) [44]. The avatar evokes importance and confidence (key components of motivation) with MI strategies such as identifying pros of behavior change, providing affirmations to reinforce “change talk” and boost confidence, and identifying strengths and resources. MI strategies are utilized within the motivational enhancement system to promote autonomy, boost self-efficacy, and identify social supports, while also addressing stigma and coping. The intervention manages “counter-change talk” by having the avatar reflect without judgment and provide statements to emphasize autonomy. As with interaction with a human counselor, interactions are synchronous and not reliant on feedback at the completion of the session. Small amounts of education about PrEP are integrated with motivational elements. The intervention is branched, with participants assigned to different branches based on their rating of importance of PrEP and their confidence in taking it; each branch has content tailored to these responses. For example, participants who give a low rating to the importance of PrEP are assigned to a branch that focuses on decisional balance exercises, while those who give a high rating for importance are assigned to a branch that provides reinforcement. The participants are placed in branches that provide content exploring stigma, autonomy, self-efficacy, and social supports. Participants are given feedback on their PrEP knowledge and information on the protective effects of PrEP adherence. Each participant is then asked to set a goal: obtain a PrEP prescription, maintain optimal adherence, practice steps, or think about it more, and asked to identify possible barriers to usage (such as stigma, forgetting, or side effects) and form plans for overcoming these barriers. In the second session (1 month later), participants are assigned to new branches based on whether they met their goal (this branch provides reinforcement and encourages planning for continued success), partially met their goal (this branch focuses on identifying plans for overcoming barriers), or did not meet their goal (this branch reviews the importance of PrEP and encourages confidence in it). The participants may choose a new goal or continue the same goal.

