#### Phase II: Pilot MOST Design-Based Trial (R33)

We will launch a pilot trial using a full factorial design to evaluate the feasibility, acceptability, and preliminary efficacy of intervention components to increase PrEP uptake and adherence among young Thai transgender women. The trial will examine (1) the effect of each component on participants who are currently on PrEP but not adherent and participants who have not started PrEP and (2) whether the presence or absence of a component has an impact on the performance of other components. While there exist several approaches to construct a MOST trial, we will use a full factorial design given its relative simplicity and cost efficiency [48,51]. For our MOST trial, the 2 intervention components each have 2 levels, resulting in a 2^1^2^1^ full factorial with 4 experimental conditions. MOST requires a well-defined optimization criterion. We will use PrEP uptake and adherence as the measure of success. In order to build an optimized intervention for participants who are on PrEP and participants who are not on PrEP, we will enroll 80 participants who are on PrEP and 80 participants who have not started PrEP. The 80 participants who have not started PrEP will all be individuals who are at high risk and are eligible for PrEP but have not yet decided to start PrEP.

Standard PrEP counseling will be provided to all participants at the beginning of the trial and treated as a constant component in the experiment. After counseling, participants will be randomly assigned to 1 of the 4 experimental conditions (Table 1). Separate randomization for participants who are on PrEP and participants who have not started PrEP will be conducted via Qualtrics (Qualtrics XM). The primary outcome will be PrEP uptake and adherence assessed through computer-assisted self-interviewing (CASI) and dried blood spot (DBS) testing. The main effects of the intervention components and the interactions between them will be estimated using ANOVA. The goal of the R33 phase is to examine intervention strategies based on preliminary effect sizes, feasibility, and acceptability and prepare for a fully powered randomized controlled trial to evaluate the optimized intervention package.

**Table 1 table1:** Study experimental conditions.

Experimental condition (n=20 for each condition)	Standard PrEP^a^ counseling	Motivational enhancement system for PrEP	Enhanced YaCool
1	Yes	Yes	Yes
2	Yes	Yes	No
3	Yes	No	Yes
4	Yes	No	No

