### Data Analysis

#### Intervention Evaluation

We will estimate retention rates, overall and per condition, and examine differences across conditions using the chi-square test. We will assess differences in acceptability using the *t* test or the Mann-Whitney test. The minimum criteria for acceptability and feasibility will be point estimate for mean System Usability Scale score ≥50 and having at least 50% of participants respond to YaCool at least once and complete at least one MES-PrEP session [62]. Using a 2^1^2^1^ full factorial design, we will test the main effects and interactions between components with an ANOVA using effect coding (1 = “no” condition; +1 = “yes” condition) rather than dummy coding (ie, 0, 1). A participant will be classified as adherent if her tenofovir level in DBS reflects the use of TDF/FTC tablets 4 to 7 days a week over the prior 6 weeks (a level with an almost 100% preventive effect). Participants whose tenofovir levels cannot be assessed will be classified as nonadherent. The intervention effect on PrEP uptake and adherence will be further assessed using mixed-effects modeling controlling for potential confounding factors (eg, age and education) and possible baseline differences. Missing data will be handled using full information maximum likelihood estimation. Effect sizes will be estimated for the primary outcomes. All analyses will be conducted using the SAS 9.4 statistical software package (SAS Institute Inc).

Structural equation modeling will be used to examine the extent to which the targeted variables (eg, information, motivation, and self-efficacy) mediate the intervention effect. Guided by our conceptual model, we will assess the effects of intervention on the mediator and the effects of the mediator on the outcome, controlling for other mediators and confounders, and we will then estimate the proportion of the intervention effect explained. Mediation models will be tested using MPlus (Muthén & Muthén). Given the limited sample size, conclusions from the mediation analyses will be limited and treated with caution, but modeling will allow us to explore the constructs of IMB and potential predictors in preparation for a larger efficacy trial.

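### The month-1 self-report directly follows MES-PrEP session 2, yet its 4-week adherence item covers only days before that session

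*Protocol article*

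**What the plan says.** Data Collection Tools and Procedures places the first follow-up computer-assisted self-interview (CASI) "immediately postintervention at the end of the first month", with later rounds at 3, 6, 9 and 12 months. One of its adherence items asks: "What percentage of the time were you able to take all your PrEP medications in the past 4 weeks". The same section also lists a visual analog adherence interview, for which no recall window is given, and a dried blood spot (DBS) measure.

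The MES-PrEP Intervention section describes two sessions. On the second it says: "In the second session (1 month later), participants are assigned to new branches based on whether they met their goal". For participants who did not reach their goal, "this branch reviews the importance of PrEP and encourages confidence in it"; the other branches give reinforcement or work on barriers. Study Aims says the sessions are completed "while at clinics for this study".

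The conditions without MES-PrEP have no matching contact at month 1: "Standard PrEP counseling will be provided to all participants at the beginning of the trial". That section (Phase II) also names CASI together with DBS as the source of the primary outcome. Intervention Evaluation classifies a participant as adherent from her DBS tenofovir level over the preceding six weeks.

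The Abstract words the schedule differently. It counts all five follow-up assessments, including the one at month 1, from the end of the intervention.

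**The concern.** If the survey comes directly after session 2, the arms differ in what happens just before the adherence question. Women in conditions 1 and 2 have just discussed with the avatar whether they met their goal, and have been reinforced or encouraged accordingly. Women in conditions 3 and 4 have not. The question looks back over a period that ended when session 2 began, so session 2 can change the answer but not the behavior that the answer describes.

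At stake is the month-1 MES-PrEP contrast in self-reported adherence. Self-report is a named source of the primary outcome, and Component Selection allows a component to be kept on a medium to large effect size without statistical significance. A reporting difference between arms could therefore enter that decision if month-1 self-report is used for it.

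**Working it through.** The plan states no figure on this point, so there is none to reproduce. The check is date arithmetic and a head count.

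**Inputs**
- Session 1: day 0.
- Session 2: one month later (MES-PrEP Intervention). Taken as day s = 28, 30 or 31; this range is an assumption.
- Survey day t: equal to s under Data Collection Tools and Procedures.
- Recall window: the 28 days from t − 28 to t.
- 20 participants per condition in each of two strata of 80 (Phase II section and Table 1). MES-PrEP is given in conditions 1 and 2.

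**Formula.** Recall days after session 2 = t − max(t − 28, s).

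**Methods schedule (t = s)**

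| Session 2 and survey | Recall window | Days after session 2 | Days after session 1 |
|---|---|---|---|
| day 28 | 0 to 28 | 28 − 28 = 0 | 28 |
| day 30 | 2 to 30 | 30 − 30 = 0 | 28 |
| day 31 | 3 to 31 | 31 − 31 = 0 | 28 |

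None of the 28 days follows session 2. All 28 follow session 1, so the item can still reflect session 1 and use of Enhanced YaCool.

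**Sensitivity to the survey date.** If the survey came 7 days after session 2, 7 of the 28 days would follow it (session 2 on day 30, survey on day 37: 37 − max(9, 30) = 7).

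**Abstract schedule, read literally.** With the survey 28 to 30 days after session 2, for example s = 30 and t = 58, the count is 58 − max(30, 30) = 28. All recall days then follow session 2 and the problem disappears.

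**Later visits.** At month 3 (about day 91) the window is days 63 to 91, and with s = 30 the count is 91 − max(63, 30) = 28. The windows at months 6, 9 and 12 also lie wholly after session 2.

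**Participants.** MES-PrEP conditions: 2 × 20 × 2 strata = 80 of 160. Of these, 40 are PrEP users at enrollment and 40 have not started PrEP. Those still off PrEP at month 1 have no pill-taking to report, so 80 is an upper bound for the adherence item.

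**DBS as a cross-check at month 1.** The article does not say at which visits DBS is taken. If it is taken at month 1, its six-week window (42 days) begins 42 − 31 = 11 to 42 − 28 = 14 days before session 1. It would not cover the same period as the 4-week item, although it is not open to reporting differences.

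**The case against.** The strongest objection is that the order of tasks within the visit is inferred. The Methods phrase names a time point; no visit-level sequence is given, and a condensed article may leave that to the full protocol. The Abstract's wording, taken literally, removes the difficulty. This stands as a limit. But the Methods text does place the survey immediately after the intervention ends, and the two schedules cannot both hold, so clarification is needed either way.

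The safeguards also carry weight. The adherent classification rests on DBS, self-reports are triangulated with DBS, uptake is confirmed from charts and pharmacy records, CASI is private, and no text makes month 1 the primary time point. These confine the issue to self-reported adherence at one visit. They do not remove the difference between arms in what precedes the question.

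Some stronger readings are tempting, but the documents do not support them:
- **That the month-1 contrast is shown to be biased toward MES-PrEP.** That direction is plausible, but it is an inference. The avatar is designed to be nonjudgmental and has branches for goals partly met or unmet, so franker reporting is also possible.
- **That every adherence item has this window, or that session 2 always reviews adherence.** The 4-week period is stated for one item, and adherence is only one of four goals a participant may set.
- **That the mediation analysis runs backward in time.** Intervention Evaluation says "we will assess the effects of intervention on the mediator and the effects of the mediator on the outcome" but fixes no visit or lag for either path. A pairing of month-1 mediators with month-1 adherence is nowhere stated.
- **That the knowledge, motivation and skills scores are wrongly inflated.** These are the constructs MES-PrEP targets, and measuring them after the full course is an ordinary postintervention reading.

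Moving the adherence items also cannot undo influence on reporting from session 1, or from participants knowing what they received. It removes only the avoidable part caused by session 2.

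**Conclusion.** The point holds in a limited form. On the Methods text, 0 of the 28 recall days of the 4-week item follow session 2, while the item is asked straight after that session in the MES-PrEP conditions only. The month-1 answer cannot capture an effect of session 2 on behavior and is exposed to possible differential reporting of unknown direction and size.

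Its reach is one of five follow-up visits, self-reported adherence only, and at most 80 of 160 participants. A reader might infer that month-1 adherence is uninformative or that the primary outcome as a whole is compromised. Neither follows: the window lies wholly after session 1, the DBS classification does not depend on what participants say, and months 3 to 12 are unaffected.

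The conclusion assumes that session 2 and the month-1 survey fall on the same visit in the order the Methods wording implies. It fails if the Abstract's schedule is the intended one.

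**What to change.** 1. Reconcile the Abstract's schedule with Data Collection Tools and Procedures, stating whether the month-1 survey is counted from session 1 or from the end of session 2.
2. If it shares a visit with session 2, give the self-reported adherence items before session 2 in the MES-PrEP conditions and at the same point of the visit in the other conditions. Keep the usability scale after session 2.
3. State in the analysis text that month-1 adherence reflects session 1 plus Enhanced YaCool where assigned, and that the full two-session effect is read from month 3.
4. The knowledge, motivation and skills scales may stay where they are, since moving them would give up the immediate post-course reading. If month-1 mediators are used, relate them to adherence from month 3 onward.

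The cost is a fixed task order within one existing visit and a sentence or two of text. No visit, measure or participant is added.

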### Data Analysis

#### Intervention Evaluation

We will estimate retention rates, overall and per condition, and examine differences across conditions using the chi-square test. We will assess differences in acceptability using the *t* test or the Mann-Whitney test. The minimum criteria for acceptability and feasibility will be point estimate for mean System Usability Scale score ≥50 and having at least 50% of participants respond to YaCool at least once and complete at least one MES-PrEP session [62]. Using a 2^1^2^1^ full factorial design, we will test the main effects and interactions between components with an ANOVA using effect coding (1 = “no” condition; +1 = “yes” condition) rather than dummy coding (ie, 0, 1). A participant will be classified as adherent if her tenofovir level in DBS reflects the use of TDF/FTC tablets 4 to 7 days a week over the prior 6 weeks (a level with an almost 100% preventive effect). Participants whose tenofovir levels cannot be assessed will be classified as nonadherent. The intervention effect on PrEP uptake and adherence will be further assessed using mixed-effects modeling controlling for potential confounding factors (eg, age and education) and possible baseline differences. Missing data will be handled using full information maximum likelihood estimation. Effect sizes will be estimated for the primary outcomes. All analyses will be conducted using the SAS 9.4 statistical software package (SAS Institute Inc).

Structural equation modeling will be used to examine the extent to which the targeted variables (eg, information, motivation, and self-efficacy) mediate the intervention effect. Guided by our conceptual model, we will assess the effects of intervention on the mediator and the effects of the mediator on the outcome, controlling for other mediators and confounders, and we will then estimate the proportion of the intervention effect explained. Mediation models will be tested using MPlus (Muthén & Muthén). Given the limited sample size, conclusions from the mediation analyses will be limited and treated with caution, but modeling will allow us to explore the constructs of IMB and potential predictors in preparation for a larger efficacy trial.

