### Sample Size of Trial

Using G*power 3.1.9 (Heinrich-Heine-Universität Düsseldorf) for the ANOVA, we will set the effect size *F* at 0.35, α at .05 and the sample size at 80 (20 for each experimental condition). The calculated statistical power is 80% for detecting the 2 main effects, MES-PrEP and YaCool, and 73% for detecting their interaction. The pilot trial is not an efficacy study, and therefore is not fully powered to detect both main effects and interactions, but has a sample large enough to detect a medium to large effect size for MES-PrEP and YaCool.

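### The exploratory mediation analysis is summarised by a proportion of effect explained, a ratio that cannot be interpreted if the component effect is small; the indirect effect with an interval would serve better

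*Protocol article*

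**What the plan says.** The Intervention Evaluation section plans structural equation models for the information-motivation-behavioral skills constructs. Two paths are estimated: "we will assess the effects of intervention on the mediator and the effects of the mediator on the outcome, controlling for other mediators and confounders". The closing summary is "we will then estimate the proportion of the intervention effect explained". No indirect effect with its own interval is named.

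The same section limits the weight of the results: "Given the limited sample size, conclusions from the mediation analyses will be limited and treated with caution". It gives exploration ahead of a larger trial as the purpose.

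The Sample Size of Trial section sets the effect size "at 0.35, α at .05" and "the sample size at 80 (20 for each experimental condition". Those are inputs to the ANOVA power calculation. The trial enrols 80 PrEP users and 80 participants who have not started PrEP, and the article does not say whether the mediation models use 80 or 160.

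The candidate mediators in Data Collection Tools and Procedures are "knowledge, attitudes, motivations, and behavioral skills related to taking PrEP". Self-report is scheduled at baseline and at months 1, 3, 6, 9 and 12. A participant counts as adherent if her blood-spot level "reflects the use of TDF/FTC tablets 4 to 7 days a week over the prior 6 weeks"; one self-report measure covers the past 4 weeks. No text pairs a mediator visit with an outcome visit.

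**The concern.** A proportion explained is the indirect effect divided by the total effect. When the total effect is small relative to its standard error, the denominator can come close to zero or change sign. The ratio then becomes very large, turns negative or exceeds 1. It has no value at exactly zero and is erratic near it.

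A pilot that describes itself as not fully powered may well meet that situation. The caution in the plan concerns sample size in general. It does not tell the reader when the ratio has stopped meaning anything. At stake is what the mediation results are for, which is learning about the theoretical constructs before the larger trial. An unstable percentage is easily quoted as if it ranked those constructs.

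**Working it through.** **The plan's own figure.** The article gives no figure for mediation. Its power statement (80% for main effects, 73% for the interaction) supplies the effect size used here. With noncentrality 0.35² × 80 = 9.8 and 76 denominator degrees of freedom, the noncentral F gives 79.0% with 2 numerator degrees of freedom and 72.7% with 3. The stated figures therefore reproduce. One degree of freedom, which is what each 2×2 effect has, gives 87.1%. That is a separate matter and does not affect this point.

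**Why the denominator matters.** Each component compares 40 with 40 in one stratum. With within-arm SD 1, the standard error of the total effect is √(1/40 + 1/40) = 0.224. The effect in SD units is d = 2f.

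- f=0.35: d = 0.70, and 0.70/0.224 = 3.1 standard errors from zero.
- f=0.10: d = 0.20, and 0.20/0.224 = 0.9 standard errors from zero.
- f=0.10 with both strata pooled: the standard error is √(1/80 + 1/80) = 0.158, and 0.20/0.158 = 1.3.

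At 0.9 or 1.3 standard errors the estimated denominator is often near zero or of the wrong sign.

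**Simulation.** From the document: N=80 or 160 and f=0.35. Assumed: a true proportion of 50%, a mediator-outcome slope of 0.5, a control rate of 20% for the yes/no outcome, and the smaller effect sizes. The proportion is a × b / c, where a is the intervention-to-mediator path, b the mediator-to-outcome path and c the total effect. Each setting used 8,000 to 10,000 runs.

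| N | f | Middle 95%, continuous | Middle 95%, yes/no |
|---|---|---|---|
| 80 | 0.35 | 0.20 to 1.12 | 0.14 to 1.73 |
| 80 | 0.25 | 0.05 to 1.86 | -0.47 to 2.42 |
| 160 | 0.25 | 0.22 to 1.12 | 0.16 to 1.73 |

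At f=0.10 and N=80, 35 to 37% of estimates fall outside 0 to 1. Repeat runs at f=0.35 and N=80 moved the upper limits between 1.12 and 1.16 (continuous) and between 1.73 and 1.82 (yes/no). The yes/no limit is soft because some runs give a total effect of exactly zero. Blood-spot adherence is a yes/no outcome, so the last column applies to it.

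**Sensitivity to the assumptions.** With a true proportion of 30%, a slope of 0.4 and a continuous outcome:

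| N | f | Middle 95% | Outside 0 to 1 |
|---|---|---|---|
| 80 | 0.35 | 0.05 to 0.75 | 1.8% |
| 80 | 0.25 | -0.17 to 1.20 | 9.3% |
| 80 | 0.10 | -3.06 to 3.97 | 38.1% |
| 160 | 0.35 | 0.12 to 0.58 | 0.1% |
| 160 | 0.10 | -1.65 to 2.98 | 28.2% |

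**Effect of restricting the ratio.** In the same setting at N=80 and f=0.10, keeping only runs with a significant total effect (14.7% of runs) narrows the range from -3.06 to 3.97 down to -0.08 to 0.55. The median in those runs is 0.19 against a true 0.30, because runs that reach significance overstate the total effect. Restriction removes the absurd values but leaves some bias.

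**Timing, conditional on a same-visit model.** Suppose true mediation is zero and adherence drives the construct with within-arm correlation r. Then a = r × c and b = r, so the apparent proportion is r²: 0.25 at r=0.5 and 0.49 at r=0.7. At N=4000 the simulated medians are still 0.25 and 0.49, so this is bias and not noise. A month-1 mediator (week 4.3) would precede the 6-week window of a month-3 blood spot (week 13.0 − 6 = week 7.0). If adherence persists with correlation 0.7 (assumed) and the effect is sustained, the spurious share at r=0.5 falls to 0.25 × 0.7 = 0.175. It is reduced but not removed.

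**The case against.** The strongest reply is that the plan has already disclosed the weakness. The analysis is labelled exploratory, both paths are assessed alongside the ratio, and Component Selection relies on main effects, interactions, cost, feasibility and scalability, with no role for mediation. Reporting a product of paths with an interval could be left to the analysis plan. This stands as a reason to rate the point minor. It does not answer the point itself, because the article names the ratio as the summary, and general caution gives no rule for when to withhold it.

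A reader might infer three stronger things, and the document supports none of them.

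- *The plan can report strong mediation where there is none.* At f=0.35, N=80 and no mediation, an estimate of 30% or more arises in only 1.4% of runs. Instability alone does this often only at small total effects: 26.8% of runs at f=0.10 and 37.0% at zero.
- *Mediator and outcome are measured at the same visit.* The article does not say so, and its five post-baseline assessments allow a lag. Reverse causation is also not a fault of the ratio: testing the two paths gave false mediation in 34% of runs at r=0.5 and f=0.35. The look-back argument does not extend to uptake, which is assessed by prescription with chart and pharmacy confirmation.
- *Mediation is fitted at N=80.* The article does not fix this, so both 80 and 160 are shown above.

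**Conclusion.** The point holds as a minor improvement. The named summary is imprecise at the planned effect size and largely uninterpretable when the total effect is small; pooling both strata cures neither problem at small effects. The exact ranges rest on assumed slopes, true proportions and a control rate that the document does not give, but the breakdown at f=0.10 appears under both sets of assumptions. Visit timing is a condition to be stated and not a shown error. No decision rule in the article depends on the mediation results, so the consequence is limited to what is carried forward about the constructs.

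**What to change.** In Intervention Evaluation, replace the proportion as the mediation summary with the indirect effect of each mediator (product of the two paths, on the risk-difference or standardised scale) and a percentile-bootstrap 95% confidence interval. Report a proportion only when the confidence interval of the total effect excludes zero, and note that such selected proportions can still be biased.

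Add that, where adherence is the outcome, the mediator is taken from a visit before the 4- or 6-week look-back window, for example month-1 constructs with month-3 adherence. State whether the models use one stratum or both.

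The cost is a few sentences of analysis text and a different output request. The self-report visits are already scheduled. The article does not tie blood-spot sampling to month 3, so that pairing should be checked against the full visit schedule.
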